### Sample size and power calculations

The sample size we require in the quantitative phase to provide sufficient power was calculated as 63 persons for each group. This sample size was calculated to be adequate at an alpha of 0.05 and a power of .80, to test for a difference between the groups. we considered a potential dropout rate of 30%. According to the formula below, we should start with a recruitment target of 75 participants in each group:

In accordance with this approach, a total of 150 women at risk, aged 18 to 48, from the Tehran Municipality Health House, will be recruited using the inclusion and exclusion criteria listed in Table 1.

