### Participants

The research population will include women aged 18–48 years who are sexually active. To meet these inclusion criteria, recruitment will be from women who refer to Tehran Municipality Health House Participants will be recruited from Tehran Municipality Health House affiliated by the Women Empowerment Headquarters of Tehran Municipality. The list of introduced eligible participants will be initially contacted via phone and given an in-depth description of the study, those interested will be followed up with an inclusion listing. Once Tehran Municipality Health House has received a briefing about the project and understands the randomized controlled trial design and data collection elements of the study, it will be asked to sign the consent form and allocate one room for the research project. Invitations to participate in the study will be stretched to all eligible women until we reach a sample size of 150 women who provide informed consent to participate. Table 1 contains a complete list of the inclusion and exclusion criteria.

**Table 1 Tab1:** Inclusion and exclusion criteria

Inclusion criteria	Exclusion criteria
• Women aged 18–48 years • Women without cervical cancer • Women without mental disorders, drug dependence, and addiction • Tend to participate with informed consent to share information, and participate	• Absence of more than two sessions in training sessions • The participant has a special illness that is not able to participate in training sessions

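### Recruiting 75 women per arm leaves about 52 after the stated 30% dropout, not the 63 that the 80% power requires

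*Protocol article*

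**What the plan says.** The protocol article, under Sample size and power calculations, gives the requirement for the quantitative phase: the number needed "was calculated as 63 persons for each group". It ties that number to its error rates: "This sample size was calculated to be adequate at an alpha of 0.05 and a power of .80". It then allows for attrition and sets the target per arm: "we considered a potential dropout rate of 30%. According to the formula below, we should start with a recruitment target of 75 participants". The paragraph closes with "a total of 150 women at risk, aged 18 to 48", and the section Participants repeats the total, with invitations continuing "until we reach a sample size of 150 women who provide informed consent to participate". The Abstract also gives 150. The total is therefore consistent across the article, and 75 per group is not an isolated misprint.

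The dropout formula that the paragraph points to is not in the text at hand. The paragraph states no effect size, standard deviation, outcome or sidedness.

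**The concern.** An allowance for dropout is meant to leave the required number of evaluable participants after the loss has occurred. Here the required number (63), the loss (30%) and the recruitment target (75) are all printed, and the third does not follow from the first two. If the 30% allowance is used up, the trial has fewer completers than its own calculation requires, and the printed 80% power does not apply.

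At stake is the chance of detecting the difference the trial was designed for, and how a non-significant result is understood by a reader who takes the 80% at face value. Attrition is a live risk in this plan. The section Engagement and retention describes the participants as hard to keep in a study. The Discussion lists loss at the later assessments and a low questionnaire response as limitations. Table 1 also lists missing more than two training sessions as an exclusion criterion.

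**Working it through.** **Inputs from the protocol article**
- Required per arm: 63; alpha 0.05; power 0.80; dropout 30%; recruited per arm 75, total 150 (Sample size and power calculations).
- Allocation 1:1 (Trial design).
- Outcomes are mean scores (Hypothesis).

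**Assumptions, not in the article:** a two-sided test and a two-group comparison of means at the standardised difference d that 63 per arm implies.

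**1. Can 63 be reproduced?** Normal approximation: n per arm = 2 x (1.960 + 0.842)^2 / d^2. With d = 0.50 this is 62.8, so 63. The t-test version gives 63.8. The base figure therefore fits d of about 0.50, but that value is inferred.

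**2. Can 75 be reproduced from 63 and 30%?**
- n / (1 - dropout) = 63 / 0.70 = 90.
- n x (1 + dropout), a common mistake: 63 x 1.30 = 81.9, so 82.
- n / sqrt(1 - dropout) = 63 / sqrt(0.70) = 75.3. This non-standard form comes close and may be the source of 75, but it does not preserve 63 completers.

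**3. What dropout does 75 support?** 1 - 63/75 = 0.16, so 16%. Under the mistaken multiplier, 75/63 - 1 = 0.19, and a 20% multiplier gives 63 x 1.2 = 75.6.

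**4. How many remain at 30%?** 75 x 0.70 = 52.5 per arm, so 52 or 53, and 105 in total against 126 required. The shortfall is 63 - 52.5 = 10.5 per arm. If each woman stays independently with probability 0.70, the chance that a given arm keeps at least 63 of its 75 is about 0.4%.

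**5. What does this do to power?** Two-sided 0.05, two-group comparison:

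| Completers per arm | t-test, d = 0.50 | t-test, d = 0.503 (exactly 80% at 63) | Normal, d = 0.50 |
|---|---|---|---|
| 63 | 79.5% | 80.0% | 80.1% |
| 53 | 72.2% | 72.8% | 73.0% |
| 52 | 71.4% | 71.9% | 72.2% |

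If the test were one-sided and 63 per arm gave exactly 80%, power would be 73.0% at 52 and 73.8% at 53 (normal approximation).

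**6. Detectable difference with 80% power.** At 63 per arm it is 0.50 SD. At 52 per arm it is 0.549 SD by the normal approximation and 0.555 SD by the t-test.

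**7. What could baseline adjustment recover?** Adjusting for the baseline score multiplies the residual variance by (1 - r^2), where r is the correlation between baseline and follow-up. The article gives no r, so this is a range of assumed values. At d = 0.50 and 52 per arm, power is about 75% for r = 0.3, 79% for r = 0.4 and 83% for r = 0.5.

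**The case against.** Four points can be made for the plan.

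- **The formula is missing from the text.** That gap comes from text extraction and is not an error in the plan. It does not help, though, because no formula can make 75 recruits leave 63 completers when 30% are lost.
- **The 30% is an allowance and not a forecast.** The article says "we considered a potential dropout rate of 30" percent, and it describes flexible session times, a free midwife visit and payment for completing questionnaires. If actual dropout stays at or below 16%, at least 63 per arm remain. This stands, and it limits the conclusion: the trial falls short only if losses exceed 16%. The statement as printed is still wrong at the rate the article chose.
- **Women who drop out late are not wholly lost.** The quantitative analysis section plans repeated-measures mixed models, which can use earlier follow-up data. Together with baseline adjustment this could recover some or all of the lost power, depending on the correlations. This stands in part. However, the sample-size paragraph rests on "an alpha of 0.05 and a power of .80, to test for a difference between the groups", credits no correlation, and inflates for dropout itself. The analysis section describes the repeated-measures comparison as within each group and calculates the between-group mean differences separately. A gain that is not written down cannot support the printed figure.
- **The loss is moderate, and a null result would be judged mainly by its confidence interval.** The plan does commit to 95% intervals for the mean differences, which softens the effect on interpretation. It does not make the three figures agree.

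**Conclusion.** The concern holds. The required 63 per arm, the 30% dropout allowance and the target of 75 per arm cannot all be true. At 30% dropout about 52 or 53 per arm remain, a shortfall of 10 or 11, and 75 per arm covers 16% dropout, about half the stated allowance. These results need only the article's own figures.

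The size of the power loss rests on assumptions: a two-sided comparison of two means, at the effect implied by 63 per arm (d about 0.50), with dropouts contributing no data. On that basis power falls from 80% to about 71 to 73%, so the chance of missing the design effect rises from 20% to about 28%. This is a moderate loss, but the stated power is wrong under the plan's own allowance and the correction is cheap, so it should be made.

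**What to change.** Keep 150 and reword the sample-size paragraph in one of two ways:

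- state that 75 per arm preserves 80% power for dropout up to 16%; or
- keep the 30% allowance and state that about 52 per arm would then remain, with power of about 72% at d = 0.50, or a detectable difference of about 0.55 SD at 80% power.

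In either case, state the effect size, the outcome and the sidedness behind 63, and print a dropout formula that matches the target. If credit is claimed for a baseline-adjusted between-arm analysis, name that analysis in the plan and show power over a range of correlations (such as 75%, 79% and 83% at r = 0.3, 0.4 and 0.5), or leave the credit out.

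The section Trial design should be reconciled at the same time. It sets its contingency at failing to recruit 63 women, without saying whether that is per arm, and it refers to a discussion of the impact that the sample-size section does not contain.

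The cost is a few reworded sentences and a less favourable stated power or dropout allowance, with no extra participants. The alternative that keeps both 80% power and 30% dropout is 90 per arm, 180 in total, which is 30 more women than planned.

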### Randomization and blinding

After informed consent and baseline data collection, participants in the randomized controlled trial will be randomly assigned to the intervention and control arms in a restricted randomized block design. A research identification number will be given to each woman. Then, the identified individuals who volunteered to participate in the study were randomly assigned to the experimental and control groups using a blocking method. Following simple randomization procedures, participants will be assigned to one of two trial arms in a 1:1 ratio based on a computerized randomization program via https://www.sealedenvelope.com/simple-randomiser/v1. The letter A will be considered for the intervention group1 and the letter B for the control group. The process of random allocation will be continued continuously until the sample size will be reached. Masking of participants and study staff is not possible due to the nature of the intervention (educational) and allocation ratio. The first researcher ([name]) will enroll participants in the study and allocate them a unique ID number. A statistic expert out of the research team ([name]) will generate the allocation sequence using the women’s numbers. The first researcher ([name]) will then inform women which group they have been allocated to.

### Engagement and retention

As this is a group of participants that can be particularly difficult to participate and maintain in a study, given the sensitive nature of STIs, several steps will be taken to optimize retention. These include scheduling training at maximally convenient times for participants, hiring a trained midwifery that will be flexible and attentive to the individual’s needs, and frequent opportunities for questions and feedback. In addition, for a free visit, a trained midwifery will coordinate for a genital examination, and the names of the intervention group will be announced to the specialist.

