### Trial design

The evaluation design is a parallel, randomized controlled trial, with two arms and with a 1:1 allocation ratio. The intervention arm will receive the training program starting in June 2022, and the control arm will receive the training program after the final research data collection, with training from June 2023. If the trial is not able to recruit 63 women within the recruitment period, then the research team will consider an unequal allocation ratio with a smaller number of participants in the control group or extending data gathering time. The impact of this is discussed in the section on sample size.

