## Methods

### Aim, design, and outcomes

This practical randomized trial aims to evaluate the impact of an educational program based on the ISD model on improving preventive behaviors of STI Iranian women. An exploratory sequential mixed-methods design will be used in the study.

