### Outcome measures

The initial research questions addressed in this study are “Does the educational intervention based on Instructional System Design (ISD) model affect STI preventive behaviors among Iranian women?”. To answer this main question following primary outcomes are expected:Determining and comparing the effects of an educational intervention designed based on the ISD model in STI knowledge among women in the target and control groups before, immediately one month, and three months after the interventions.Determining and comparing the effects of an educational intervention designed based on the ISD model in STI vulnerability among women in the target and control groups before, immediately, one month, and three months after the interventions.Determining and comparing the effects of an educational intervention designed based on the ISD model in STI prevention self-efficacy among women in the target and control groups before, immediately, one month, and three months after the interventions.Determining and comparing the effects of an educational intervention designed based on the ISD model in STI prevention intentions among the target and control groups before, immediately, 1 month, and 3 months after the interventions.

Consequently, we expect the effect of our educational intervention on preventive action regarding STIs among women. To assess the expected secondary outcomes a self-reported assessment addressing preventive actions (using a condom, doing pap-test and genital examination) will be conducted.

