### Strategies to improve adherence to interventions

Women are required to be present at the study site in person to receive the intervention, and any missed sessions are recorded to check adherence. To improve adherence, training program times are flexible between 9am and 5pm each day (room availability permitting), are not required to be at the same time of day, and are not required on weekends. Participants will be arranged for a free visit with a trained midwife for genital examination and health counseling.

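### The genital-examination item of the secondary outcome is confounded by a free examination visit that the trial itself arranges and links to the intervention group

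*Protocol article*

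**What the plan says.** Outcome measures (Protocol article) defines the secondary outcome: "a self-reported assessment addressing preventive actions (using a condom, doing pap-test and genital examination) will be conducted". Genital examination is one of the three actions listed.

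The same examination appears twice as a service provided by the trial:

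- Strategies to improve adherence to interventions: "Participants will be arranged for a free visit with a trained midwife for genital examination and health counseling". No arm is named.
- Engagement and retention: "a trained midwifery will coordinate for a genital examination, and the names of the intervention group will be announced to the specialist". Here the arrangement is tied to the intervention group.

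Aim, design, and outcomes states what is being tested, namely to "evaluate the impact of an educational program based on the ISD model on improving preventive behaviors of STI Iranian women". The free visit is not named there as a component. Trial design says that "the control arm will receive the training program after the final research data collection". No section gives controls the visit during follow-up, and none says how an examination arranged by the study is to be counted.

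**The concern.** The study supplies, free of charge, the act that it later counts as an outcome, and on the natural reading it does so for one arm. Removing cost and access barriers can raise examination rates even if the teaching changes nothing. As the item is defined, an examination that a woman sought herself and one that the study booked for her score the same.

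At stake is the interpretation of this one item. A difference in favour of the intervention could not be attributed to the ISD programme. The item still matters, because the self-reported actions are the trial's only measure of what women did; the four scales cover knowledge, vulnerability, self-efficacy and intentions. Masking gives no protection: "Masking of participants and study staff is not possible due to the nature of the intervention (educational) and allocation ratio".

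**Working it through.** The protocol states no figure on this point, so there is none to reproduce. The check has two parts.

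**1. Sections side by side.**

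- Outcome measures counts the genital examination.
- The adherence section arranges it for participants, under a heading about adherence to the intervention.
- The retention section sends the intervention group's names to the specialist.
- Trial design and The intervention programs serve controls only after the final assessment.
- No section excludes, flags or separately counts trial-arranged examinations.

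Followed as written, the plan mixes free access with any educational effect on this item.

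**2. How large the effect could be (illustration only).**

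Inputs from the protocol: 63 per group and alpha 0.05 (Sample size and power calculations). Sidedness is not stated there; two-sided is assumed.

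Inputs assumed, because the protocol gives neither:

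- p0, the background examination rate in both arms
- u, the share of otherwise unexamined intervention women who use the free visit

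Education is set to have no effect, and controls are not offered the visit. The intervention-arm rate is then

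p1 = p0 + u(1 − p0).

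With p̄ = (p0 + p1)/2 and n = 63, the chance of a significant difference is

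Φ( [ (p1 − p0) − 1.96·√(2p̄(1 − p̄)/n) ] / √([p0(1 − p0) + p1(1 − p1)]/n) ).

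Worked case, p0 = 0.10 and u = 0.30:

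- p1 = 0.10 + 0.30 × 0.90 = 0.37 and p̄ = 0.235
- numerator: 0.27 − 1.96 × 0.0755 = 0.122
- denominator: √((0.0900 + 0.2331)/63) = 0.0716
- ratio about 1.70, so the chance is about 96%

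Each cell below gives the intervention-arm rate, then the chance of a significant result:

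| Background p0 | u = 10% | u = 20% | u = 30% | u = 50% |
|---|---|---|---|---|
| 10% | 19%; 30% | 28%; 74% | 37%; 96% | 55%; >99% |
| 20% | 28%; 18% | 36%; 52% | 44%; 83% | 60%; >99% |
| 30% | 37%; 13% | 44%; 37% | 51%; 67% | 65%; 98% |
| 50% | 55%; 8% | 60%; 20% | 65%; 40% | 75%; 83% |

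The nominal rate is 5%. Every cell exceeds it, but the excess ranges from slight to near-certain, depending on two rates that the protocol does not give.

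**3. Would simply excluding trial-arranged visits solve it?** No. Some intervention women who would have been examined anyway may use the free visit. With a 10% background rate, if 30% of those women switch, the count without trial-arranged visits is 0.10 × (1 − 0.30) = 7% in the intervention arm against 10% in controls. That is a deficit for the intervention when there is no true effect.

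**The case against.** **The visit may be meant for both arms.** The adherence section says participants without naming an arm, and the retention section does not say in terms that controls are excluded. If both arms had equal access and uptake, the differences in the table would not arise. However, the adherence section concerns women receiving the intervention, and the only group named in connection with the specialist is the intervention group, so an arm-linked offer is the natural reading. Even with equal access, the study would still partly produce the outcome: a true difference in examination rates would shrink by the factor (1 − u). The ambiguity is a reason to reconcile the sections, not evidence of a flat contradiction.

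**The visit may be part of the package.** That is a legitimate design, and the visit is stated in advance. But the text presents it as an adherence and retention device and attributes effects to the education. If it is part of the package, the plan should say so.

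**Education may itself lead women to take up the visit.** This stands. The visit is not described as compulsory, so a higher rate would be confounded, not wholly artefactual.

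**Stronger readings that the documents do not support.**

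- A reader might infer that the whole secondary outcome is compromised. Only one of the three actions is directly produced by the visit. Condom use is not, and nothing says that Pap tests are taken at it.
- A reader might infer that the visit's counselling biases the four primary scales. That is possible, but the text gives no basis for asserting it.
- A reader might infer differential dropout. That too is conjecture: the Discussion proposes payment for completing questionnaires without limiting it to one arm, and controls are promised the programme later.

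**Conclusion.** The point holds in a narrow form. One of three self-reported actions in the secondary outcome is confounded by a free visit that the trial arranges and links to the intervention group. A higher examination rate in that arm could partly reflect free access rather than the ISD education.

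The conclusion rests on the wording of the sections and on reading the offer as arm-linked. Its size cannot be fixed from the documents. At 30% uptake the chance of a significant result with no educational effect runs from about 40% to 96% over background rates of 50% down to 10%; at 10% uptake it runs from about 8% to 30%. These figures depend on assumed rates and show only that the problem need not be negligible.

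**What to change.** 1. Add one questionnaire item, or cross-check the midwife's list, to record whether each reported examination was the study's free visit.
2. Report examinations by arm in total and split into trial-arranged and not trial-arranged. Do not credit the total to education alone.
3. Treat the count that excludes trial-arranged visits as a sensitivity analysis, not as the sole definition, because it is biased against the intervention when women who would have been examined anyway use the free visit.
4. Reconcile Strategies to improve adherence to interventions with Engagement and retention on which arm is offered the visit, and state whether the visit is part of the tested intervention. That choice is the sponsor's.

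Withholding arm labels from the specialist would not help here: the outcome is self-reported, and who receives a free appointment would be unchanged.

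The cost is one extra item or a list check, some wording, and a more cautious, less favourable reading of the examination result. Sample size, randomisation and the educational content are unaffected.

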### Data analysis

#### Phase 1 (qualitative analysis)

To carry out the qualitative content analysis process, each interview’s audio file will be listened to carefully several times on the same day and transcribed verbatim. In order to keep the data from the interviews private, each transcript will be assigned a code. To come up with the overall impression of the interviews and become fully immersed in the data, the audio files and transcripts will be reviewed several times, and any ambiguities and inconsistencies will be removed by comparing the audio files and the transcripts. The interviews will be audiotaped and a summary of the key points of each interview will be then sent to each participant to ensure that the interviewer will have interpreted that participant’s comments accurately [39]. The process of data analysis will be performed continuously and simultaneously with the data gathering process. All words, statements, and paragraphs that are relevant to the analysis process will be considered as a single semantic unit. After merging the semantic units, the codes will be extracted. The codes are combined to form subcategories, which are then combined to form the main categories. Finally, after the categories have been abstracted, the relevant themes will be identified [40]. The data will be managed using MAX.QDA-ver2020.

